### Sample size

2.4

Sample size estimates are based on the mean and standard deviation of the Pittsburgh sleep quality index^[13]^ scores of patients after 8 weeks of treatment, referencing the pre-test results of 11.24 ± 5.03 for the treatment group and 14.27 ± 5.31 for the control group, set at α = 0.025, one-sided test, β = 0.20. Calculated by PASS 15.0 software to require 47 participants per group. With an estimated drop-out rate of 10%, 53 patients will be included in each group.

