### Recruitment strategy and distribution plan

2.5

Participants will be screened among patients attending outpatient clinics and recruitment information will be disseminated through the distribution of brochures and posted on the Internet and WeChat platforms to widen the scope of screening. Participants who meet the inclusion criteria will be fully informed of the purpose and protocol of the study and informed consent signed by the participants will be obtained.

The study will randomly assign patients who meet the criteria for either the treatment group (Baduanjin exercise group) or the control group (Western medicine group) in a 1:1 ratio through a central network-based randomization tool. The random numbers are generated by a statistician using a computer software program and these random numbers are placed in sealed opaque envelopes which are handed to the participants by the study coordinator. Due to the specific nature of the intervention, the patient and the operating physician are knowledgeable about the assigned outcome. However, the assessors of the study results and the statisticians who counted and analyzed the data are unaware of the allocation.

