### Outcomes

2.7

(1)Pittsburgh sleep quality index^[13]^: including sleep quality, time to sleep, sleep duration, sleep efficiency, hypnotic medication, sleep disturbance, and daytime functioning. After scoring respectively, the total score is 21. The higher the score, the worse the sleep quality.(2)Hamilton Depression Rating Scale^[14]^: it includes 24 items. The higher the score, the heavier the symptoms.(3)Incidence of adverse reactions: including treatment-related discomfort experienced by patients during the study period.

Two research assistants who are unclear about the outcome of the subgroups will score the 2 groups of patients according to outcome indicators before treatment, at the end of treatment, and at month 1 and month 3 of the end of treatment, through outpatient visits.

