### Statistical analyses

2.9

Independent statisticians with unclear results for random assignment will be responsible for the statistics and analysis of the data, and the data collected will be statistically analyzed by SPSS 20.0 software. The chi-square test will be used for count data; mean ± standard deviation ($\bar{x}\pm \text{S}$) will be used for measurement data, independent samples *t* test for normal distribution and Mann–Whitney *U*-test for skewed distribution, and differences will be considered statistically significant at *P* < .05.

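### The stated comparison of arms names no baseline covariate although baseline scores are collected; prespecifying ANCOVA would gain precision at no extra data cost

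*Protocol article*

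**What the plan says.** Section 2.7 (Outcomes) of the protocol article has PSQI and the Hamilton Depression Rating Scale scored "before treatment, at the end of treatment, and at month 1 and month 3 of the end of treatment", so every randomised patient should have a baseline value on both scales.

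Section 2.9 (Statistical analyses) summarises measurement data as mean and SD and compares arms by "independent samples *t* test for normal distribution and Mann–Whitney *U*-test for skewed distribution", with significance at P below .05. It names no covariate, change score or repeated-measures model, and gives no rule for deciding which distribution applies.

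Section 2.4 (Sample size) works from PSQI "scores of patients after 8 weeks of treatment", taking "pre-test results of 11.24 ± 5.03 for the treatment group and 14.27 ± 5.31 for the control group", "set at α = 0.025, one-sided test, β = 0.20". The result is 47 per group, raised to 53 for 10% drop-out.

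**The concern.** The patient's own starting score is often a useful predictor of a later score on the same scale. A two-sample test on the later score alone leaves the variation explained by baseline in the error term. ANCOVA removes it and needs no further patients, visits or measurements. The trial is planned at 80% power with no margin, and its Discussion concedes a small sample, so any free precision is worth having.

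The second feature is that the test follows the shape of the observed data. The comparison may then be of means for one scale or visit and of ranks for another, and which it will be is not known until the data are seen.

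At stake is the width of the confidence interval and the chance of detecting the planned difference. The validity of the trial is not in question.

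**Working it through.** **Inputs from section 2.4.** Week-8 PSQI 11.24 (SD 5.03) and 14.27 (SD 5.31); one-sided α 0.025; β 0.20. Allocation is 1:1 (section 2.5).

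**Input not in the documents.** The correlation r between baseline and week-8 PSQI. It is assumed, over a range of 0.2 to 0.6.

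**Step 1: reproduce the plan's figure.**
- Difference: 14.27 − 11.24 = 3.03.
- Pooled SD: √((5.03² + 5.31²)/2) = 5.172. Standardised effect: 3.03/5.172 = 0.586.
- Standard error at 47 per arm: 5.172 × √(2/47) = 1.067. Noncentrality: 3.03/1.067 = 2.84.
- Noncentral t with 92 degrees of freedom: power 80.2%. At 46 per arm it is 79.4%, so 47 is the smallest size that reaches 80%.
- Drop-out: 47/0.9 = 52.2, rounded up to 53.

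Both stated figures reproduce, and they belong to an unadjusted two-sample t test on post-treatment scores. The one-sided 0.025 level has the same critical value as a two-sided 0.05 test, which is how the P below .05 of section 2.9 is read here.

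**Step 2: the same design with ANCOVA.** Adjustment for baseline multiplies the error SD by √(1 − r²) and costs one degree of freedom (91 instead of 92). Example at r = 0.5: residual SD 5.172 × 0.866 = 4.479; standard error 4.479 × √(2/47) = 0.924; noncentrality 3.03/0.924 = 3.28; power 90.1%.

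| Assumed r | Residual SD | Power at 47 per arm | Interval narrower by | Per arm for 80% power |
|---|---|---|---|---|
| unadjusted | 5.172 | 80.2% | – | 47 |
| 0.2 | 5.067 | 81.8% | 2% | 45 |
| 0.3 | 4.934 | 83.8% | 5% | 43 |
| 0.5 | 4.479 | 90.1% | 13% | 36 |
| 0.6 | 4.138 | 94.0% | 20% | 31 |

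The interval column is 1 − √(1 − r²).

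**Step 3: if change scores were meant.** With equal SDs at baseline and week 8 (an assumption), the variance of a change relative to the raw score is 2(1 − r): 1.6 at r = 0.2, 1.0 at r = 0.5 and 0.8 at r = 0.6. The ANCOVA factor 1 − r² is 0.96, 0.75 and 0.64 at the same values. ANCOVA is more precise than change in each case, and change is worse than the raw score when r is below 0.5.

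**Step 4: does the switch between tests inflate error?** A null simulation used 47 per arm and 8,000 runs, with scores rounded and held within 0 to 21. A Shapiro-Wilk test at 0.05 in each arm decided between the t test and the Mann-Whitney test. Type I error was 0.0495 for roughly normal scores and 0.047 for skewed scores, so there is no inflation.

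**The case against.** The strongest reply is that nothing here is wrong. With random 1:1 allocation an unadjusted comparison is unbiased, the sample size was computed for that comparison, and the two agree. That stands, and it limits the point to lost precision.

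The size of the gain also rests on a correlation that the documents do not give. At 0.2 it is only 1.6 percentage points of power (81.8% against 80.2%). The Hamilton entry threshold of at least 24 (section 2.3.2) restricts the baseline range and may lower the correlation for that scale. The power figures here are for PSQI only. All of this stands.

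It can also be said that a condensed article leaves covariates to an analysis plan. This carries less weight, because section 2.9 does commit to named tests and to a way of choosing between them. The suggestion concerns that stated method.

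Four stronger readings are tempting and not supported:
- **That a Mann-Whitney result would leave no mean difference to set against 3.03 points.** Section 2.9 reports mean and SD for measurement data, so arm means remain available whichever test gives the P value.
- **That the Mann-Whitney test takes power below 80%.** A loss of that kind applies to normal data, for which the plan uses the t test.
- **That choosing the test from the data inflates false positives.** The simulation shows no such effect.
- **That chance baseline imbalance undermines the result.** Its size depends on a baseline SD that is not given, only the part correlated with outcome carries over, and the unadjusted standard error already allows for it.

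**Conclusion.** The point holds as a free improvement. The planned analysis is valid and has its stated 80% power on the trial's own assumptions, but it names no use of baseline scores that are collected anyway. For PSQI at 47 per arm, ANCOVA would raise power from 80.2% to between 81.8% (r = 0.2) and 94.0% (r = 0.6), with intervals 2% to 20% narrower. The benefit is slight at the low end and substantial from about 0.5 upward.

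This rests on the assumed correlation and on reading the tests as applied to post-treatment scores. The sample size basis supports that reading, but section 2.9 does not state it. If changes were meant, baseline is used, though less efficiently than by ANCOVA. The surviving objection to the switch is that the test, and whether it compares means or ranks, is not fixed in advance.

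**What to change.** In section 2.9, prespecify one main analysis for both PSQI and the Hamilton score: a linear model of the week-8 score on arm and the baseline score of the same scale (ANCOVA). A mixed model over the post-treatment visits, with baseline, arm, visit and arm-by-visit, read at week 8, would serve equally. Report the adjusted mean difference with its 95% confidence interval. Keep the Mann-Whitney test as a sensitivity analysis, in place of the switch on observed distribution.

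The cost is one paragraph. SPSS fits both models, and no patients, visits or measurements are added. The sample size can stay at 53 per arm, since the unadjusted calculation is then the conservative one for any correlation in the range shown.

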## Discussion

3

The development of depression is related to a variety of factors, including genetics, social relationships, and neurobiology.^[15,16]^ Insomnia is not only a symptom of depression, but also affects a person's mood and behavior, increasing the risk of developing depression,^[17]^ and some studies have shown^[18]^ that insomnia patients are far more likely to develop depression than the general population. Therefore, it has been suggested that treating depression and insomnia together results in better overall symptom improvement for patients than treating depression alone.^[19]^

Baduanjin exercise is a traditional Chinese exercise that can improve the function of the internal organs of the body by regulating the flow of Qi and blood through the meridians to achieve the effect of fitness and dispel diseases.^[20]^ At present, Baduanjin exercise has been widely used in the treatment of diabetes mellitus,^[21]^ chronic obstructive pulmonary disease,^[22]^ and heart failure,^[23]^ and has achieved good results. Clinical studies have found that Baduanjin exercise improves the symptoms of depressed patients by regulating the expression of lncRNA, mRNA, and circRNA,^[24]^ and are also effective in improving sleep quality.^[25]^ There are no rigorous clinical studies to verify whether the same efficacy of Baduanjin exercise exists in patients with both depression and insomnia. Therefore, this study evaluates the efficacy and safety of Baduanjin exercise in the treatment of depression with insomnia through a rigorous randomized controlled protocol to provide a clinical basis for its dissemination.

Due to the small sample size and the regionalization of the included population, the results may be affected to some extent; Although this study was followed up for 3 months, it may still be impossible to objectively evaluate the long-term effect of Baduanjin exercise on patients with depression and insomnia. We look forward to more metacenter and large sample randomized controlled studies to verify our conclusions.
